### Secondary Outcome Measures

#### Smoking Rates

Among smokers, the proportion of people who have quit smoking will be compared for the 2 groups.

#### Change Over Time in Other Psychosocial and Attitudinal Measures

Change over time in scores on the GAD-7, WHO-5, and SF-12 and in self-efficacy and readiness to change behaviors and emotions will be compared between the self-directed and supported groups using repeated-measures analysis of variance. Multiple regression analysis, with groups entered as potential predictors, will be used to predict participants with greatest improvements in GAD-7, WHO-5, SF-12, and self-efficacy scores, and readiness to change behaviors and emotions.

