**Methods:**

People who have experienced a cardiac event in the previous 12 months and have access to the internet will be eligible for this study (N=120). Participants will be randomly assigned to one of the two study conditions: either “self-directed” completion of the *Back on Track* program (without assistance) or “supported” completion of the *Back on Track* program (additional 2 telephone sessions with a lifestyle counselor). All participants will have access to the web-based *Back on Track* program for 2 months. Telephone sessions with the supported arm participants will occur at approximately 2 and 6 weeks post enrollment. Measures will be assessed at baseline, and then 2 and 6 months later. Outcome measures assessed at all 3 timepoints include dietary intake, physical activity and sitting time, smoking status, anxiety and depression, stage of change, and self-efficacy in relation to behavioral and emotional self-management, quality of life, and self-rated health and well-being. A demographic questionnaire will be included at baseline only and program acceptability at 2 months only.

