### Objectives

The aim of this study is to assess the benefits, in terms of behavioral and emotional well-being, of the web-based *Back on Track* self-management program, and to test whether participants obtain enhanced benefit through the provision of one-on-one telephone support from a trained lifestyle counselor (supported arm), over and above benefit obtained through completing the web-based program alone (self-directed arm). By including 2 follow-up assessments, one on postprogram completion (2 months) and one at 4 months post program (6 months postenrollment), we aim to assess both immediate and sustained benefits.

We hypothesize that participants randomly allocated to each arm of the trial will show significant improvement in their behavioral and emotional well-being, self-efficacy, and self-rated health from the preprogram to postprogram assessments, with benefits sustained 4 months after program completion. We also hypothesize that participants allocated to the supported program will demonstrate superior improvements in behavioral and emotional well-being, self-efficacy, and self-rated health compared to those allocated to the self-directed arm, at both the postprogram and follow-up assessments.

Ethical approval was granted by the Deakin University Human Research Ethics Committee (2019-438). This project has been funded by the HCF Research Foundation. This study will be conducted and reported in accordance with the CONSORT-EHEALTH guidelines [50].

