### Data Analysis

In evaluating outcomes, there will be two groups of participants based on the mode of delivery: “self-directed” and “supported.” All statistical analyses will be performed on an intention-to-treat (ITT) basis with *P*<.05. In the case that ITT produces a null finding, it is possible that this is due to participants in the supported group not participating in the additional telephone sessions (that is, not receiving the intended treatment). To test that hypothesis, we will then undertake treatment-received analysis (also called Per Protocol) whereby only those who received the treatment in accordance with the protocol are included. This will enable us to determine whether any differences were obtained between those who received the self-directed treatment and those who received the supported treatment. *P* values less than .05 will be considered significant for the primary outcome and those less than .01 will be considered significant for secondary outcomes. The effect of the intervention on the primary and secondary outcomes at 6 months will be assessed using analysis of covariance (ANCOVA) models that include the baseline value of the outcome as a covariate and the group assignment (self-directed versus supported) as a categorical variable. The treatment effect, its effect size (Hedge g), and 95% CIs for the treatment effect and within-group changes from baseline to 6 months will be calculated from the ANCOVA models. The sensitivity of the results to missing data will be evaluated using a data-based multiple imputation procedure.

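### Most secondary scores get two unranked between-arm analyses (6-month ANCOVA and repeated-measures ANOVA), and the hypothesised 2-month difference has no baseline-adjusted estimate

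*Protocol article*

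**What the plan says.** The Data Analysis section states: "The effect of the intervention on the primary and secondary outcomes at 6 months will be assessed using analysis of covariance (ANCOVA) models". These models "include the baseline value of the outcome as a covariate and the group assignment (self-directed versus supported) as a categorical variable". The treatment effect, Hedges g, confidence intervals and within-group changes all come from them, for baseline to 6 months. The same section sets a threshold of .01 for secondary outcomes.

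The subsection on change over time in psychosocial and attitudinal measures then takes "Change over time in scores on the GAD-7, WHO-5, and SF-12 and in self-efficacy and readiness to change behaviors and emotions" and says that these "will be compared between the self-directed and supported groups using repeated-measures analysis of variance". That list covers every secondary outcome except smoking. The subsection also adds a multiple regression to predict who improves most, with group among the candidate predictors.

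The Objectives hypothesise improvement within each arm from before to after the program, and superiority of the supported arm "at both the postprogram and follow-up assessments", that is, at 2 and at 6 months. The abstract gives the schedule: "Measures will be assessed at baseline, and then 2 and 6 months later". On missing data, the Data Analysis section says: "The sensitivity of the results to missing data will be evaluated using a data-based multiple imputation procedure".

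**The concern.** Two between-arm analyses are fixed for the same scores, and no sentence says which one decides. They can disagree, because one estimates a difference at 6 months and the other tests a pattern over three visits. A reader of the results could not tell whether the reported analysis was the intended one.

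The second analysis also fits the hypothesis poorly. Its group main effect averages in the baseline visit, where randomised arms should not differ. Its group-by-time test does not say at which visit the arms differ. ANCOVA would give that answer with baseline adjustment, but it is specified at 6 months only, so the 2-month superiority hypothesis has no baseline-adjusted estimate.

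Finally, classical repeated-measures ANOVA needs all three visits. It therefore leaves out people whose 6-month score is available but whose 2-month survey is not.

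**Working it through.** **The plan's own figure.** Inputs from Sample Size and Power: effect size 0.55, 80% power, alpha .05 (two-sided assumed), 12% attrition.

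- n per arm = 2(1.960 + 0.842)² / 0.55² = 51.9, so 52.
- 52 / 0.88 = 59.1, so 60 per arm and 120 in total. The stated figure reproduces.
- The exact t-test needs 53 per arm. This is also the expected number of completers (60 × 0.88 = 52.8) and is used below.

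**The two analyses side by side.**

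| | ANCOVA | Repeated-measures ANOVA |
|---|---|---|
| Scores | all secondary outcomes | all except smoking |
| Visits | 6 months, adjusted for baseline | change over baseline, 2 and 6 months |
| Effect size and interval stated | yes | no |
| Named as deciding the .01 test | no | no |

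**Dilution of the group main effect.** For arm differences of (0, 0.55, 0.55) at the three visits, the main effect estimates (0 + 0.55 + 0.55)/3 = 0.37.

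**Power at alpha .01.** Assumptions: SD 1 at each visit, the same correlation r between all visits, 53 per arm, and a 6-month difference of 0.55. The documents give no r, so a range is shown.

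- ANCOVA, two-sided t test on 103 df: squared noncentrality = (53/2) × 0.55² / (1 − r²) = 8.016 / (1 − r²).
- Group-by-time F test on 2 and 208 df: λ = (53/2) × Σ(δ − mean δ)² / (1 − r), where δ is the arm difference at each visit.
 - Sustained effect (0, 0.55, 0.55): the sum is 0.2017, so λ = 5.344 / (1 − r).
 - Gradual effect (0, 0.275, 0.55): the sum is 0.15125, so λ = 4.008 / (1 − r).

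| r (assumed) | ANCOVA, 6 months | Group-by-time, sustained | Group-by-time, gradual |
|---|---|---|---|
| 0.3 | 63% | 45% | 32% |
| 0.5 | 74% | 64% | 48% |
| 0.7 | 91% | 90% | 77% |
| 0.8 | 98% | 99% | 94% |

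For a sustained effect the gap closes at about r = 0.7 and is marginally reversed at 0.8. For a gradual effect ANCOVA is ahead throughout.

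**Complete cases.** The plan states 12% attrition, so 120 × 0.88 = 105.6 have a 6-month score. Assume that a further share misses the 2-month survey, independently of final attrition:

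- 6% missing: 105.6 × 0.94 = 99.3, a loss of 6.3.
- 12% missing: 105.6 × 0.88 = 92.9, a loss of 12.7.

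Classical repeated-measures ANOVA would therefore omit about 6 to 13 people whom the 6-month ANCOVA keeps.

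**The case against.** The best defence is that the two methods answer different questions: a difference at 6 months, and a course over time. Only the ANCOVA is given an effect size and interval, and the .01 threshold stands in the same paragraph, so it is the natural candidate for the deciding analysis. This stands in part. The plan is not arithmetically inconsistent, and a single ranking sentence would settle the choice of result. But both methods are written as comparisons of the arms on the same scores, and the text does not rank them.

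Several stronger readings are tempting but not supported:

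- *The plan drops incomplete cases, contrary to intention to treat.* The article never says so. Deletion is a property of the classical method, imputation is planned as a sensitivity analysis of the results generally, and ANCOVA also loses anyone without a 6-month score. Only the extra loss shown above is attributable to the second analysis.
- *Only 42 to 48 of 60 per arm would remain.* That needs 20% missing at 6 months (60 × 0.80 = 48; × 0.88 = 42), whereas the plan expects 12%. The 48 is also what ANCOVA would have.
- *Variance rises by 18% to 33%.* The ratio 2/(1 + r) gives this for r = 0.7 and 0.5, but it describes a single baseline-to-6-month change contrast, not the planned three-visit test.
- *The trial loses precision.* The 6-month ANCOVA is planned in any case, and a second analysis takes nothing from it.
- *The 2-month comparison is untested.* Repeated-measures ANOVA uses the 2-month scores. What is lacking is a baseline-adjusted estimate at that visit.

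One objection changes the remedy. For these scores, repeated-measures ANOVA is the only specified analysis that treats baseline as a response, and so the only one that addresses within-arm change at 2 months. Deleting it without replacement would leave part of the first hypothesis untested.

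**Conclusion.** The point holds for the secondary scores. Two findings rest on the text alone: two between-arm analyses of the same scores have no stated order at the .01 level, and the 2-month superiority hypothesis has no baseline-adjusted estimate.

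The size of the power difference rests on assumptions. For a sustained effect it is 18 percentage points at r = 0.3, 10 at r = 0.5 and about 1 at r = 0.7. For a gradual effect it is 31, 26 and 14 points at the same correlations. These figures assume equal correlations between visits and apply the planning effect size of 0.55 to secondary scores, for which the plan states no effect of their own. The 6 to 13 omitted participants depend on the classical form of the method and on an assumed 2-month missing rate.

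The stated sample size is unaffected. The change should be made because it is nearly free and removes the choice between results, not because the present plan invalidates the trial.

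**What to change.** For the continuous secondary scores, replace the repeated-measures ANOVA with one mixed model for repeated measures:

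- **Responses:** the 2- and 6-month scores.
- **Fixed effects:** baseline score, visit, arm, arm-by-visit and baseline-by-visit.
- **Covariance:** unstructured.
- **Participants:** all randomised participants with at least one follow-up score, analysed as randomised.
- **Ranking:** the 6-month arm contrast is decisive at .01, and the 2-month contrast is supportive. The model takes the place of the separate 6-month ANCOVA for these scores, so that one result per score decides.
- **Within-arm hypothesis:** report changes from baseline at 2 and 6 months from the same model, or from a constrained version with baseline as a response.
- **Missing data:** keep multiple imputation as the sensitivity analysis.

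Analyse the 5-point readiness item with an ordinal counterpart. The dichotomised primary outcomes and smoking are outside this change and need their own models.

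The cost is wording and slightly more analysis work. No new data are needed and the sample size does not change. People with no follow-up score at all still do not contribute to the model, so the imputation analysis remains necessary.

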### Assessing the Back on Track Program Acceptability

Proportions will be calculated for all items on the program acceptability scale.

## Results

Recruitment began in May 2020 and concluded in August 2021. A total of 122 participants were enrolled in this study. Data collection, including 2- and 6-month follow-up is expected to be completed by February 2022, and data analysis and publication of results will be completed by June 2022.

## Discussion

With cardiac event survivors at a heightened risk of a recurrent events and premature death, and with suboptimal attendance at center-based rehabilitation and secondary prevention programs, there is a need for innovative eHealth programs to support people in their behavioral and emotional self-management after an acute cardiac event. We anticipate that the *Back on Track* program will assist people in their recovery after an acute event and will represent a flexible, easily accessible, user-friendly, and effective adjunct to center-based programs. Our findings will enable us to quantify the behavioral and emotional improvements obtained and sustained for people with CHD who participate in the *Back on Track* program, while also comparing two methods of delivery: one fully self-directed and the other supported by a lifestyle counselor**.**

## Abbreviations

AAS: Active Australia Survey
ACHH: Australian Centre for Heart Health
AMI: acute myocardial infarction
ANCOVA: analysis of covariance
CABGS: coronary artery bypass graft surgery
CBT: cognitive-behavioral therapy
CHD: coronary heart disease
CR: cardiac rehabilitation
DQT: Diet Quality Tool
GAD-7: 7-item Generalized Anxiety Disorder instrument
IPAQ: International Physical Activity Questionnaire
ITT: intention to treat
MI: motivational interviewing
NHFA: National Heart Foundation of Australia
PCI: percutaneous coronary intervention
PHQ: Patient Health Questionnaire
PICF: participant information consent form
RCT: randomized controlled trial
REDCap: Research Electronic Data Capture
SF-12: Short Form Health Survey
WHO-5: World Health Organization–Five Well-Being Index
